### Assessment

Since PCC can affect different domains of functioning, measurements were chosen based on an integral vision of health and include body function impairments, activity limitations, and participation restrictions as well as personal factors, according to the *International Classification of Functioning, Disability and Health* [7]. All variables will be measured by daily diary items, validated questionnaires, and physical examination (Figure 1 and Tables 1-3). Based on design standards, the recommended minimum number of baseline measurements in an R-SCED study is 5 [30]. In this study, daily diaries will be completed for 7 to 10 days (baseline measurements) in phase A. In addition, there are 40 measurements during the rehabilitation treatment and a minimum of 7 to 10 follow-up measurements. The validated self-administered questionnaires will be collected at the start of phase A (T0), at the end of phase B (T1), and after 3 months of follow-up (T2). Participants will complete the questionnaires and the daily measurements with an app (YourResearch) on a computer or mobile device.

**Table 1 table1:** Overview of the secondary outcome measurements: body function.

Secondary outcome measurements	Measurement instrument	T0^a^	T1^b^	T2^c^
Muscle strength	Muscle strength is a commonly used test for physical function [31]. A Jamar HHD^d^ is used for handgrip muscle strength [32,33]. Muscle strength of the knee extensor or flexor is measured using a dynamometer (Biodex System 3 Pro Dynamometer) [34].	✓	✓	
Fatigue	MFIS^e^: this is a 21-item metric for fatigue severity. A total score is calculated as the sum of the subscale scores (0-84). Higher scores indicate higher levels of fatigue [35].	✓	✓	✓
Breathlessness	MRC^f^ breathlessness scale: ranging from 1=no trouble with breathlessness to 5=I am too breathless to leave the house [36].	✓	✓	✓
Pain	NRS^g^: mean pain intensities in the last 7 days, ranging from 0 to 10 [37].	✓	✓	✓
Cognitive function	CFQ^h^: this is a 25-item self-report questionnaire. The total scores range from 0 to 100, with higher scores reflecting a report of more frequent cognitive errors in everyday life [38,39].	✓	✓	✓

^a^T0: beginning of baseline phase (phase A).

^b^T1: after completion of the treatment phase (phase B).

^c^T2: after completion of the follow-up phase.

^d^HHD: handheld dynamometer.

^e^MFIS: Modified Fatigue Impact Scale.

^f^MRC: Medical Research Council.

^g^NRS: Numerical Rating Scale.

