### Sample Size Calculation

Experience from previous single-case experimental design (SCED) studies showed that the sample size varies between 6 and 27 participants [54-56]. One of our earlier prospective cohort studies was used in calculating the sample size. In this study, the USER-P was the primary outcome and improved in the first year after ICU discharge, [8]. In this cohort, the effect size based on changes in the level of participation appeared to be medium from baseline to 12 months follow-up (>0.5), with a statistical power of >0.8. Using the calculation tool developed by Bouwmeester and Jongerling [57] for SCED studies, with a medium effect size, the number of measurements, and accounting for loss-to-follow-up, 20 patients need to be included in this study. Patients withdrawn from the study will not be replaced. All analysis will be performed according to the “intention-to-treat” principle.

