Missing data will be handled according to the randomized-marker method, in which all days of the diary that were not completed will be displayed as “N/A” (not applicable) [63].

For the other primary outcome measurements (USER-P and EQ-5D-5L) and the secondary outcome measurements, the results on T0, T1, and T2 will be computed as total scores on each questionnaire individually. Outcomes will be presented in mean (SD) or median (IQR), depending on the distribution. Outliers will be checked, defined as values more than 3 times the IQR from the median. The statistical analysis of the questionnaires will use repeated measures ANOVA in case of normal distribution or the Friedman test in case of nonnormal distribution. The statistical analysis of the physical examination will use the paired 2-tailed Student *t* test in case of normally distributed variables or the paired Wilcoxon test in case of nonnormally distributed variables. The significance level was set at *P*=.05, 95% CI. The statistical analysis will use IBM SPSS statistics version 26. No imputation will be made for missing data.

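### Under an intention-to-treat promise, the questionnaire tests in standard form use only patients with all three visits; this costs precision and can bias USER-P and EQ-5D-5L results in either direction

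*Protocol article*

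**What the plan says.** Under Sample Size Calculation the article states: "All analysis will be performed according to the “intention-to-treat” principle". The same paragraph says that loss to follow-up was allowed for, without giving a rate, and that withdrawn patients are not replaced.

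Under Statistical Analysis the questionnaires are handled apart from the diaries: "For the other primary outcome measurements (USER-P and EQ-5D-5L) and the secondary outcome measurements, the results on T0, T1, and T2" are computed as total scores. The method is then fixed: "The statistical analysis of the questionnaires will use repeated measures ANOVA in case of normal distribution or the Friedman test" (the latter for nonnormal data). The missing-data rule for this part is "No imputation will be made for missing data", and the software is fixed too: "The statistical analysis will use IBM SPSS statistics version 26".

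The diaries have their own provisions, a multilevel analysis and a separate rule: "Missing data will be handled according to the randomized-marker method". Neither is extended to the questionnaires.

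**The concern.** Classical repeated measures ANOVA and the Friedman test both work on a complete patient-by-visit table. Without imputation, a patient with a gap at any one of the three visits drops out of the whole analysis. The patient most likely to be affected is one who completes treatment, fills in T0 and T1, and does not return the T2 questionnaires 12 weeks later. That patient's change over the treatment period is known but is not used.

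The result is an analysis of patients with complete data, which does not deliver what the intention-to-treat statement leads a reader to expect. At stake are two outcomes that the article calls primary, in a sample of 20 where each lost patient is 5% of the data. If the reason for missing T2 is related to how the patient responded, the T0–T1 change among completers also differs from the change in all patients.

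**Working it through.** **Inputs from the article.** N = 20; three questionnaire visits (T0, T1, T2); repeated measures ANOVA or Friedman; no imputation; no replacement; loss to follow-up allowed for but with no rate. All missingness rates, correlations and odds ratios below are assumptions.

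**The planned N.** The figure of 20 came from a calculation tool for single-case designs whose settings are not reported, so it cannot be reproduced. The point does not depend on it.

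**Step 1: patients left in the analysis.** With T0 complete and missingness p, independent at T1 and T2, the expected number analysed is 20 × (1 − p)², and the chance of keeping all 20 is (1 − p)⁴⁰.

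| p per visit | Expected number analysed | Chance of keeping all 20 |
|---|---|---|
| 5% | 20 × 0.9025 = 18.1 | 13% |
| 10% | 20 × 0.81 = 16.2 | 1.5% |
| 15% | 20 × 0.7225 = 14.5 | 0.2% |
| 20% | 20 × 0.64 = 12.8 | 0.01% |

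**Step 2: precision.** The standard error of a mean change is SD/√n. If 4 of 20 lack only T2, the complete-case T0–T1 analysis has n = 16 although 20 changes were observed: √(20/16) = 1.118, a standard error about 12% larger than necessary.

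**Step 3: power of the three-visit test.** Take effect f = 0.25 and within-patient correlation 0.5. The noncentrality is n × 3 × f²/(1 − 0.5).
- n = 20: 20 × 3 × 0.0625/0.5 = 7.5, power 0.65.
- n = 16: 16 × 3 × 0.0625/0.5 = 6.0, power 0.54.

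**Step 4: bias, first scenario.** True change 0.30 SD at T1 and T2; correlation 0.6; T0 and T1 complete. T2 is missing with log-odds −1.6 ± 1.2 × (T0–T1 change, centred and standardised). This gives about 22% missing and about 15.6 completers of 20. The slope is an odds ratio of e^1.2 = 3.3 per SD of change, a strong dependence.

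| Who misses T2 | T0–T1 change, completers | T0–T1 change, all observed values |
|---|---|---|
| Poor responders | 0.49 | 0.30 |
| Good responders | 0.11 | 0.30 |
| Completely at random | 0.30 | 0.30 |

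If the change is not centred in the first row, about 17% are missing and completers give 0.45.

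**Step 5: bias, second scenario.** True change 0.50 SD; correlation 0.5; 20% missing T2. Poor responders leaving at odds ratios of 2 to 4 per SD gives completer T0–T1 changes of 0.63 to 0.72 and T0–T2 changes of 0.56 to 0.61. Good responders leaving at odds ratio 4 gives 0.28 for T0–T1. Completely random missingness gives 0.50. A likelihood-type analysis of all visits gives 0.50 at both times in each of these cases.

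**Step 6: limit of the remedy.** If missing T2 depends on the unseen T2 value itself (odds ratio 3 per SD worse; 20% missing; true 0.50), the likelihood-type analysis gives 0.63 for T0–T2 and completers give 0.59. Neither is right.

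**The case against.** The article nowhere says that patients with a missed visit are excluded. That follows from how the named tests normally work. The study has one arm, so there is no randomised comparison for dropout to unbalance, and intention-to-treat can be read as keeping patients whatever their adherence. Declining to impute is not the fault either, since the mixed model proposed here imputes nothing. This is fair: the defect lies in the choice of test combined with the absence of imputation. It does not rescue the plan, because even on the loose reading a patient with observed T0 and T1 values should stay in the T0–T1 comparison, and the named tests do not allow that.

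A reader might infer that the plan will overstate benefit because patients who do badly are the ones who leave. The documents do not support this. They give neither a dropout rate nor reasons for dropout, and the reverse pattern understates benefit just as readily. Questionnaires are completed in an app, and the payment of €75 is tied to finishing the diaries and all questionnaires (Ethical Considerations). Both may keep missingness low.

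A reader might also object that both tests are global over three visits and that no contrast is named. Pairwise changes with intervals can follow a repeated measures ANOVA, the article mentions 95% CIs, and naming contrasts is commonly left to an analysis plan not shown here. That is not part of this point.

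**Conclusion.** The point holds for the questionnaires: the named tests, without imputation, give a complete-case analysis of USER-P, EQ-5D-5L and the secondary questionnaires planned at all three visits, despite the stated principle. Some loss of precision is certain once anyone misses a visit: about 12% on the standard error if 4 of 20 lack T2. Bias is a possibility whose direction and size cannot be known from the article. The range from 0.11 to 0.49 around a true 0.30 rests on one assumed scenario with strong dependence of dropout on response; with completely random missingness there is no bias. The daily diaries are not affected, nor are the physical tests, which are measured at T0 and T1 only and compared in pairs. The change should be made because two primary outcomes are involved and the remedy is cheap.

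**What to change.** For the questionnaires measured at T0, T1 and T2, replace repeated measures ANOVA/Friedman by a linear mixed model:
- restricted maximum likelihood, with time as a three-level factor;
- one covariance structure named in advance, and a small-sample degrees-of-freedom method such as Satterthwaite or Kenward–Roger;
- all available T0, T1 and T2 values, so that every patient with at least one value contributes;
- T0–T1 and T0–T2 changes reported with 95% CIs, and a bootstrap interval (resampling patients) if residuals are clearly nonnormal.

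State the number of patients with data at each visit. Add a simple sensitivity analysis, because the model assumes data missing at random: for example, lower the unseen T2 values by a range of amounts δ. The mean T0–T2 change then moves by the missing share times δ. With 4 of 20 missing and δ = 0.5 SD (illustrative), that is 0.2 × 0.5 = 0.10 SD.

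The cost is a few sentences and a different procedure in the software already planned; no new data are needed. The downside is that the model does not remove bias when missingness depends on the unseen T2 value, which is why the sensitivity analysis is needed. The article places analysis after the end of data collection, so the change should be recorded before the questionnaire data are analysed.

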### Data and Safety Monitoring

The risks attached to participating in this study are negligible and, in any case, no greater compared with other interdisciplinary rehabilitation treatments. A data safety and monitoring board has been appointed from de Clinical Trial Center Maastricht, with expertise in clinical trials. Monitoring includes informed consent forms, source data verification, and serious adverse events.

## Results

This study was funded in June 2022. The institutional review board of Maastricht University Medical Centre, University of Maastricht, approved this study in July 2023. Participant recruitment started in October 2023 and was completed in July 2024. Data collection for this study is expected to be completed by January 2025. The analysis will be conducted after data collection has been completed. It is expected that the results will be published in spring 2025.

## Discussion

### Expected Findings

This study will assess the effectiveness of a new person-oriented interdisciplinary rehabilitation treatment in patients with PCC.

The WHO and other international guidelines recommend an interdisciplinary rehabilitation treatment for long-lasting complaints due to PCC with high level of disability [9-11,23]. Although the number of studies evaluating (interdisciplinary) rehabilitation treatments for PCC has increased [12,13,17], knowledge regarding the effect of these rehabilitation treatments on participation levels and HRQoL is still limited. It is expected that this personalized interdisciplinary rehabilitation treatment for patients with PCC, who perceive high levels of disability in daily activities and participation, will improve their level of participation and HRQoL and that physical, mental, and cognitive complaints will decrease.

Next, it is expected that this interdisciplinary rehabilitation treatment, when proven effective, can be implemented in other rehabilitation centers in the Netherlands and beyond. At the same time, we anticipate that patients and health care professionals will be satisfied with the interdisciplinary rehabilitation treatment. Depending on the results of the study, the interdisciplinary rehabilitation treatment can be further improved, based on information derived from a study of the experiences of patients and health care professionals. In addition, further research is necessary regarding the cost-effectiveness of the treatment, and when proven effective, further implementation studies will be facilitated to implement the program in current rehabilitation health care in the Netherlands and beyond. The results of the study will be published in peer-reviewed journals and presented at international conferences.

### Strengths and Limitations

One strength of the study is its interdisciplinary approach. Various interventions (among others, physical training, energy management, breathing techniques, and psychological interventions) that may be effective in the treatment of PCC have been combined into a single interdisciplinary rehabilitation treatment program. Each patient is treated with a biopsychosocial approach aimed at improving physical and mental resilience and optimizing participation in society. Patients with PCC can experience various complaints such as fatigue and physical, mental, and cognitive complaints [5,64]. Patients included in this study experience high levels of disability in daily activities and low levels of participation, but the combination of their complaints may differ. An interdisciplinary rehabilitation treatment with a biopsychosocial approach tailored to a patient’s complaints and goals, and which takes into account personal and contextual factors, therefore seems promising.

Another strength of the study is the chosen design: SCED [65]. Randomized controlled trials (RCTs) are seen as the gold standard for evaluating treatment effectiveness [66]. However, RCTs are time-consuming, and SCEDs seem to be a good alternative [67]. SCED studies are characterized by multiple measurements in a few participants, which allows a small sample size, whereas RCTs are based on a few measurement moments in many participants. Each patient functions as its own control and SCEDs are considered to be more compatible with clinical practice than an RCT [65,68]. A SCED can result in strong internal and external validity [65]. This study aims to evaluate the effect of a person-oriented interdisciplinary rehabilitation treatment, which makes a SCED most appropriate.

One limitation of the study is that a SCED may be resource intensive. The need for detailed observation and repeated measurements for a single participant can be demanding. A second limitation in using a SCED may be the generalizability of results. Since the focus is on a single participant or a small group, it may be hard to generalize the results to larger and more diverse populations. However, this interdisciplinary rehabilitation treatment was developed for a selected population, that is, patients with high levels of disability in daily activities and participation due to PCC. This selected group is a good fit for the design of a SCED study. Nevertheless, making conclusions about the effectiveness of the treatment in patients with less severe complaints needs further consideration. More research will be needed regarding the characteristics of patients who are more likely to benefit from the treatment.

### Conclusions

To our knowledge, this will be the first study to investigate the effect of an interdisciplinary rehabilitation treatment with a person-centered, biopsychosocial approach, to aim at improving social participation and HRQoL for patients with PCC. Our findings will help to improve the treatment and support of patients with PCC.

## Appendix

Multimedia Appendix 1 Daily diary, English translation.

Multimedia Appendix 2 Peer-Review version 1 (including feedback on patient information letters and other medical-ethical documents) from the medical-ethical review board of Maastricht University Medical Centre, University of Maastricht.

Multimedia Appendix 3 Peer-Review version 2 (including feedback on patient information letters and other medical-ethical documents) from the medical-ethical review board of Maastricht University Medical Centre, University of Maastricht.

## Abbreviations

ACT: acceptance and commitment therapy
CBT: cognitive behavioral therapy
COPM: Canadian Occupational Performance Measure
HRQoL: health-related quality of life
ICU: intensive care unit
MDC: multidisciplinary consultation
PCC: post–COVID-19 condition
RCT: randomized controlled trial
R-SCED: replicated and randomized single-case experimental design
SCED: single-case experimental design
USER-P: Utrecht Scale for Evaluation of Rehabilitation-Participation
WHO: World Health Organization
